## Abstract

**Background::**

Prostate cancer is the most diagnosed cancer in Black/African American men (AA) and the second‑leading cause of cancer-related deaths. A prostate-specific antigen (PSA) blood test is an early detection screening tool for prostate cancer, but uptake of PSA screening remains low among AA men. Greater PSA screening rates among AA men, coupled with earlier treatment, may reduce disparities in prostate cancer outcomes, including mortality. The current pilot study will test the first-of-its-kind mobile health (mHealth) app to improve prostate cancer knowledge and increase PSA screening uptake among AA men using home-based screening methods.

**Methods::**

AA men aged 55 to 69 and are not up to date with PSA screening will be randomly assigned 1:1 to receive a prostate cancer screening app: Prevention Taskforce App (Taskforce App; control condition) or the Prostate Cancer Genius App (Genius App; intervention condition), which was developed specifically for AA men.

**Results::**

We will evaluate the preliminary efficacy of the apps via post-intervention group differences on the validated 18-item Prostate Cancer Knowledge Scale (primary outcome). We will also explore post-intervention group differences in perceived engagement, accessibility, and acceptability between the apps. Finally, we will derive preliminary estimates of PSA screening rates between study conditions and identify mechanisms of screening adherence.

**Discussion::**

mHealth apps offer promise to improve prostate cancer knowledge and screening rates among AA men. Demonstrating the preliminary efficacy of the Genius App will support future fully-powered mHealth interventions to address health disparities.

## Introduction

1.

Disparities in prostate cancer incidence and mortality for AA men have persisted for almost half a century and are among the most extreme disparities of all cancers in the United States (US) [1]. Compared to national estimates, AA men in Oklahoma are disproportionately affected by prostate cancer incidence (104.5 per 100 k vs. 165.3 per 100 k) and mortality (19.1 per 100 k vs. 42.8 per 100 k) [2]. The prostate-specific antigen (PSA) blood test is an early detection screening measure for prostate cancer [3,4]. Approximately 30 % of the variation in mortality rates from prostate cancer can be attributed to the accessibility of the PSA test [5], but AA men are less likely to have screened with a PSA test compared to non-Hispanic White men nationally [6] and in Oklahoma [7]. Greater PSA screening uptake among AA men may reduce the disparate mortality burden of this disease [8,9]. While concerns about overdiagnosis and overtreatment of low-risk tumors from PSA screening remain, AA men benefit most from screening as they exhibit higher PSA levels, earlier disease progression, and are more likely to harbor genomically aggressive prostate cancer [2,6]. As such, recent guidelines [10] now recommend PSA screening for AA men and acknowledge that existing guidelines were developed from clinical trials that included predominantly White men and, thus, did not reflect racial and ethnic disparities in prostate cancer incidence and mortality in the US [11].

Knowledge about prostate cancer and the potential benefits of screening remain low among AA men compared to other racial groups [12]. Further, the PSA test is often completed within clinics, limiting access to AA men without a registered primary care provider, health insurance, reliable transportation, or sufficient time with a busy work or family schedule [13–16]. Increasing prostate cancer knowledge and accessibility to the PSA test could potentially be an important intervention target to reduce prostate cancer disparities among AA men. Prostate cancer education and/or screening interventions for AA men are often designed to be delivered in community-based settings, such as churches and barbershops [17–22]. However, localized interventions targeted at specific segments of the AA population lack the reach and scalability needed to have a nationwide impact on prostate cancer disparities. With the ubiquity of smartphones [23], mobile health (mHealth) apps are an effective modality to deliver highly scalable and remote interventions for prostate cancer screening and early detection. A past systematic review identified commercially available apps to promote informed decision-making about prostate cancer screening [24]. However, none of the apps included sufficient information to meet the American Cancer Society’s Early Detection Guidelines [25] and most were inactive or outdated. Furthermore, most apps were not tested within a randomized clinical trial and thus present substantial methodological limitations when evaluating their potential efficacy. No apps have been explicitly designed to promote PSA screening among AA men (e.g., using culturally sensitive language and tailored imagery). Past studies have demonstrated that culturally tailored interventions are more effective at increasing patient knowledge and intentions to screen for cancer [26,27]. Yet, there remains an opportunity to develop mHealth interventions that combine tailored information for AA men (i. e., about their greater risk for prostate cancer) with strategies that increase the accessibility of PSA screening kits.

At-home cancer screening tests have been used extensively for other cancers (e.g., fecal immunochemical tests for colorectal cancer) [28,29], and within AA communities [30–32], but at-home screening for prostate cancer has received limited investigation [33]. No existing apps integrate the ability to order an at-home PSA test and provide step-by-step navigation to complete the test. Therefore, this pilot project will test the preliminary efficacy of a prostate cancer screening app (Genius App) designed to improve prostate cancer knowledge and provide tailored screening navigation for AA men in Oklahoma. The Genius App includes several culturally responsive features to overcome limitations present in existing prostate cancer screening apps and sustain engagement. Such features include culturally tailored language and medical illustrations of AA men, testimonial videos from AA survivors, and the ability to schedule a call with a survivor from the local community to discuss prostate cancer screening and receive social support. The Genius App capitalizes on momentary changes in motivation to screen by offering on-demand ordering of at-home PSA test kits, a novel approach that could significantly impact screening rates among AA men in Oklahoma.

## Method

2.

AA men (*N* = 80), aged between 55 and 69, and who are not up to date with PSA screening according to recommended United States Preventive Services Taskforce (USPSTF) guidelines [17], will be randomly assigned 1:1 to one of two study conditions: the Taskforce App (control condition) or the Genius App (intervention condition). The Taskforce App [34] condition includes an educational app previously developed by USPSTF and the U.S. Department of Health & Human Services, a study app that includes study assessments, and a button to order an at-home PSA test. All participants will receive a study-provided, pre-paid smartphone (Samsung Galaxy S21). Both conditions will complete a baseline survey, use their respective smartphone app for 30 days, complete four once-weekly smartphone surveys, complete a one-month post-intervention survey, and be asked to complete a semi-structured exit interview after their post-intervention survey. The Genius App (see Fig. 1 in Supplemental Materials for app comparisons) will use responses to weekly smartphone surveys to guide tailored navigation content for the at-home PSA test. The study launched in February 2023 during Black History Month and is currently enrolling participants. The University of Oklahoma Health Sciences Center (reference number: 14666) institutional review board approved the protocol presented in this study. This trial was registered at ClinicalTrials.gov (NCT05331638).

### 2.1. Inclusion/Exclusion criteria

Individuals will be included in the study if they: (1) live in Oklahoma, verified via a driving license or addressed mail; (2) self-identify as “male” and “Black or African American”; (3) self-report no previous diagnosis of prostate cancer; (4) self-report have not completed a PSA test or digital rectal exam (DRE) within the past two years; and (5) self-report are between the ages of 55 and 69. Age criteria were restricted to this range to match the USPSTF guidelines and information in the Taskforce App.

### Study recruitment and procedure

2.2.

Participants will be recruited using flyers posted in predominately AA organizations (e.g., barbershops and churches), digital flyers posted on social media platforms (e.g., Facebook, Instagram, and Twitter), and via an online clinical trial recruitment company (BuildClinical). Those who scan the QR code on recruitment flyers or click the link on social media platforms will complete a brief online screener survey using the web-based Research Electronic Data Capture [35] (REDCap) platform to determine study eligibility. REDCap is a secure, HIPAA-compliant web-based application designed for data collection and consenting participants for research studies. Research study staff will contact adults who qualify for the study and schedule a phone consultation to discuss study participation. To reduce the likelihood of fraudulent enrollments in the study, participants must provide a picture of their valid driver’s license or mail with their name and proof of address.

Those deemed eligible and willing to participate during the enrollment phone call will be provided with information about the study’s purpose, goals, and procedures and asked to electronically sign a consent form and a HIPAA 1 form. To do so, participants ‘sign’ a digital version of both forms in REDCap. To do so, participants will receive a unique REDCap link and sign an e-consent instrument for the IRB-approved document. After completing the enrollment call, the participant will be granted access to their REDCap baseline survey, which can be completed on any internet-connected electronic device. After completing the baseline survey, the research team will mail a welcome packet, physical copies of the signed study forms, and a pre-paid smartphone (Samsung Galaxy S21), with the INSIGHT^™^ app downloaded onto the phone, to the participant’s home address. All participants are required to use a study-provided smartphone.

Once the participant receives the phone, they will be instructed to complete an activation assessment in the INSIGHT^™^ app. This activation assessment determines if the participant can fully utilize the app’s capabilities. Participants who pass the activation assessment are randomly assigned to receive either the Taskforce App or the Genius App conditions. Access to both apps is granted using a unique code texted by the research team to the participant. Once participants enter the unique code on the home screen of the INSIGHT^™^ app, they will gain access to the features available in their study app (i.e., Taskforce App or Genius App). Participants assigned to the Taskforce App condition are required to download the educational app and are provided extra instructions on how to do so from the Google Play Store. Once downloaded, the educational app is easy to use and navigate. Participants enter their height, weight, age, sex, tobacco use, and sexual activity history and are given screening recommendations based on those characteristics. Due to the study’s eligibility criteria, participants will receive access to prostate cancer screening information. The research team will schedule a second phone call with participants after they complete the activation assessment to ensure they entered their unique code correctly and have access to their study app content and surveys. Participants who do not pass the activation assessment will be withdrawn from the study prior to randomization and required to return the study smartphone via a return mailing package. Upon entering a correct study code, participants will use their assigned app(s) for 30 days and complete a weekly survey for four weeks [36] during the study period. After using the app for 30 days, participants will be granted access to their REDCap post-intervention survey and asked to schedule their exit interview with a research team member. Once the REDCap post-intervention survey and exit interview have been completed, the participant will return the study materials to the research team using a study-provided return mailing package (see Fig. 2 in Supplemental Materials for participant flow).

### Study randomization

2.3.

Participants (*N* = 80) will be assigned using stratified randomization to one of two study conditions: the Taskforce App (*n* = 40) or the Genius App (n = 40). Participants will be stratified on family history of prostate cancer (yes/no) and reading level (> 8th grade vs. ≤ 8th grade; based on scores on the Rapid Estimate of Adult Literacy in Medicine – Short Form [37]) to ensure that both study conditions are balanced on important factors associated with prostate cancer knowledge and screening [38–41]. An online baseline survey will be administered before randomization, and a post-intervention survey will be administered immediately after the intervention.

### Mobile health platform

2.4.

The INSIGHT^™^ Mobile Health Platform, developed by the mHealth Technology Shared Resource at the NCI-designated Stephenson Cancer Center [42], enables researchers to deploy technology-based assessments and interventions. Participants will use a study-provided smartphone (Samsung Galaxy S21) with cellular service to access study apps and complete all study activities.

### Study conditions and app features

2.5.

See Table 1 for more details about the features included in the study apps. Below is a brief description of each app and its associated features.

#### Taskforce app

2.5.1.

The Taskforce App is free on Google Play and Apple App Stores [17]. It is a practical resource designed to help health professionals and patients identify and prioritize appropriate screening based on USPSTF recommendations. The app provides screening recommendations based on characteristics input by the user and provides generic information about prostate cancer and screening.

#### On-demand app features

2.5.2.

In addition to using the TaskForce app, participants assigned to this study condition use a companion app housed on the INSIGHT^™^ mHealth Platform. On the home screen of their companion app, the following menu options can be assessed at any time during study participation by clicking on their respective button on the home menu.

##### What is the US prevention taskforce app.

2.5.2.1.

This feature provides an overview of the TaskForce App and instructions for accessing it on their study phone.

##### Order a home-based PSA test kit.

2.5.2.2.

Participants can order an imaware^™^ PSA test kit from their mailing address and navigate to register for health insurance if they are currently uninsured.

##### Report my PSA test result.

2.5.2.3.

Participants can report the results from the imaware^™^ PSA test kit PSA test or if they choose to go to a provider and complete a clinic-based PSA test.

##### Track my rewards.

2.5.2.4.

Participants can track the compensation they have earned after completing study assessments (see Compensation section).

##### Report a problem.

2.5.2.5.

Participants can report any problems encountered during study participation via an encrypted email sent directly to the research team, who typically respond within 24 h during business days (Mon-Fri).

#### Prostate cancer genius app

2.5.3.

The design of the Genius App is informed by our preliminary studies and established theoretical frameworks. The Genius App includes the following on-demand features:

##### Read the prostate cancer e-book.

2.5.3.1.

Participants have access to eight learning modules created specifically for AA men. A Black literacy expert-reviewed content in the modules to ensure the language was culturally tailored and medical illustrations of AA men were created to tailor the imagery. These learning modules cover various topics on prostate cancer, risk factors, screening, etc., followed by an interactive quiz that encompasses questions about the content (see Table 2 for an overview). Two new learning modules become available on Days 7, 14, 21, and 28. Modules are accessible any time after their scheduled study day release.

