#### Primary outcome

2.10.1.

The primary outcome measure is prostate cancer knowledge, assessed using the Prostate Cancer Knowledge Scale [57] administered at baseline and post-intervention surveys. The scale consists of 18 items that assess screening (6 items), risk factors (5 items), and warning signs (7 items) of prostate cancer. This scale has strong internal consistency (α = 0.80) and has been validated for AA adults. [57]

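### The post-intervention knowledge survey can be answered with app content at hand in both arms; the Genius content matches the scale more closely, so the primary difference may mix knowledge with look-up

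*Protocol article*

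**What the plan says.** Section 2.10.1 makes the Prostate Cancer Knowledge Scale the primary outcome, "administered at baseline and post-intervention surveys". It has 6 items on screening, 5 on risk factors and 7 on warning signs.

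The timing is in section 2.2. In both arms, "participants will use their assigned app(s) for 30 days and complete a weekly survey for four weeks". Then: "After using the app for 30 days, participants will be granted access to their REDCap post-intervention survey". The phone leaves the participant later still: "Once the REDCap post-intervention survey and exit interview have been completed, the participant will return the study materials to the research team".

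On the Genius e-book, section 2.5.3.1 states "Two new learning modules become available on Days 7, 14, 21, and 28", and then "Modules are accessible any time after their scheduled study day release". The note to Table 2 likewise describes on-demand access once a module has been presented.

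On the control side, section 2.2 says "Participants assigned to the Taskforce App condition are required to download the educational app". Section 2.5.1 says that this app "provides generic information about prostate cancer and screening" and that it is free in the public app stores.

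**The concern.** The hypothesis in the Discussion is that men given the Genius App will know more after the intervention. Section 2.6 also treats knowledge as a mechanism leading to PSA screening. Both uses need a score that reflects what a man has learned. If he can read the answers while completing the survey, the score also reflects what he can find at that moment.

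Because both arms have an app on the phone, look-up is possible in both. The issue is that the amount of relevant content differs by arm. Modules on risk and on screening methods (Table 2), the quizzes that follow the modules, and a video on signs and symptoms (Table 3) are available only to Genius men (Table 1). If look-up yields more correct answers from that material than from the Taskforce App, the primary contrast shifts towards Genius.

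Adjusting for the baseline score does not remove this. The baseline survey is completed before the phone is mailed (section 2.2), so baseline is taken without study content and follow-up with it.

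**Working it through.** **Step 1: is the content at hand when the survey opens?**
- Last module release: Day 28 by section 2.5.3.1, or Day 25 by the learning-module row of Table 4. The two schedules differ, but on either one all eight modules are out before Day 30.
- Survey opens: after 30 days (sections 2.2 and 2.8.5).
- Phone returned: after the survey and the exit interview (section 2.2).
- Access closed: not stated. Table 4 describes the Day 30 closing message as outlining the remaining steps; it mentions no lock.

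So every man still in the study, in either arm, has the phone when the survey opens, and no text ends access to the modules before then.

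**Step 2: the plan's own figure.** Section 2.11 gives SD 3.1, two-sided alpha 0.05, 30 per group, difference 2.3 and power 80%. A two-sample t-test with these inputs has power 80.7% (82.0% by normal approximation), and the detectable difference at 80% power is 2.28 points. The figure reproduces, so 2.3 points is a fair yardstick.

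**Step 3: size of a possible bias.** Let p be the share of men in an arm who look up answers and g the items each of them gains.

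Bias in the group difference = (p × g in Genius) − (p × g in control)

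The documents give neither p nor g, so every value below is an assumption. With a common g, the bias is f × g, where f is the Genius share minus the control share. The last column is the chance that the t-test rejects when there is no true difference, with 30 per arm, SD 3.1 and look-up treated as a simple shift of the mean.

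| f | g (items) | Bias = f × g | Bias ÷ 2.3 | Rejection rate |
|---|---|---|---|---|
| 0.10 | 1 | 0.1 | 4% | 5.2% |
| 0.10 | 4 | 0.4 | 17% | 7.8% |
| 0.25 | 2 | 0.5 | 22% | 9.4% |
| 0.25 | 4 | 1.0 | 43% | 23% |
| 0.50 | 2 | 1.0 | 43% | 23% |
| 0.50 | 4 | 2.0 | 87% | 69% |

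**Step 4: the control arm's contribution.**
- Same share, less useful control app: 0.25 × 4 − 0.25 × 2 = 0.5 point in favour of Genius.
- Equal shares and equal gains: 0.25 × 4 − 0.25 × 4 = 0.
- Control men looking up more often: 0.10 × 4 − 0.50 × 2 = −0.6, in favour of control.

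The sign therefore depends on behaviour. Richer content makes a shift towards Genius the more plausible direction, but does not settle it.

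**The case against.** A reader might infer that the test is open-book in the Genius arm alone and that the result must overstate knowledge gained. The documents do not support that. Control men keep the same phone to the same point and must install an information app on it. Step 4 shows that the bias can be zero or reversed. Payment is for completing surveys, not for correct answers (section 2.9), so there is no evident incentive to look things up. The content match is also uneven: warning signs form the largest subscale (7 of 18 items), yet no module title in Table 2 names them, and the videos are narrative testimonials that would be awkward to search mid-survey. All of this stands.

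A reader might also infer that exposure runs on indefinitely because no closing time for the survey is given. Section 2.3 places the survey immediately after the intervention, section 2.9 pays a bonus for finishing within 72 h, and the Discussion says that the team tightly controls app access. A condensed article may leave the survey window, any access cut-off and the survey instructions to the full protocol. Silence on those details is therefore not an error in itself.

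What remains is what the article does state: modules open at any time after release, and a phone kept until after the survey. If the full protocol already closes access or instructs men to answer from memory, the point is met.

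**Conclusion.** The point holds as a possible, differential bias of unknown size in the primary comparison. Both arms can consult an app during a remote survey, and the Genius content lies closer to the scale, so the difference may mix learning with look-up and may favour Genius.

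The 0.1 to 2.0 points (4% to 87% of 2.3) are illustrations of f × g and not estimates. At the low end the effect is negligible; at the high end it could produce most of the target difference unaided. The conclusion assumes that access does not end at Day 30, which the article neither states nor rules out, and that look-up is not equally productive in the two arms. It does not invalidate the design. It is worth correcting because the remedy is cheap and the affected quantity is the primary outcome.

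**What to change.** 1. In both arms, open the post-intervention survey with the same instruction: answer from memory, without consulting any app or other source. Tell control men explicitly that this includes the Taskforce App. At the end, ask whether any source was consulted.
2. Pause the Genius e-book, quizzes and videos in INSIGHT from the end of the 30-day use period until the survey is submitted. Keep the ordering, result-reporting and problem buttons active throughout.
3. For men already enrolled, tabulate look-up by arm, from logs if on-demand use is recorded (section 2.8.4 mentions time stamps only for assessments) or from self-report where it was asked, and use it in a supportive sensitivity analysis only. Keep all randomised men in the primary comparison. Dropping men flagged for module or video use would remove participants from the Genius arm alone, after randomisation, and could itself bias the result.

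Cost: one instruction, one question, a date-triggered pause in the team's own platform and a minor amendment. The sample size does not change. Genius men briefly lose the e-book, including the module on completing the at-home test; the kit's own instructions and staff help by phone (section 2.7) are unaffected. The Taskforce App is public and cannot be locked, so closure in the control arm rests on the instruction. That asymmetry should be stated when results are reported.
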